**Figure S3: Flow of study participant (incomplete)**

1. **Description of group characteristics at baseline**

For continuous variables, we will visually inspect histograms to assess whether they are normally distributed within intervention groups, with log-transformation of variables with a lognormal distribution. Population characteristics (Table 1) will be reported by intervention group as proportions, means (SD), geometric mean (geometric SD), and median (25th- and 75th percentiles) as appropriate, with corresponding group size. We will not test for group differences for reasons given by Assmann et al. [13].

Table S1: Description of baseline characteristics

| Variable | Type | Units/categories |
| --- | --- | --- |
| Age | Continuous | months |
| Age class | Binary | 12-23 months, 24-36 months |
| Sex | Binary | %males : %females |
| Height-for-age z-score | Continuous | SD |
| Weight-for-height z-score | Continuous | SD |
| Weight-for-age z-score | Continuous | SD |
| Haemoglobin concentration | Continuous | g/L |
| Anaemia status | Ordinal | *Severe to moderate anaemia:* haemoglobin concentration <89g/L; *mild anaemia:* haemoglobin concentration 90-109g/L; *non-anaemic:* haemoglobin concentration ≥110g/L |
| Plasma ferritin concentration | Continuous | μg/L |
| Iron status | Nominal | *Deficient:* plasma ferritin concentration <12 µg/L regardless of presence or absence of infection or inflammation; *replete:* plasma ferritin concentration ≥12 µg/L in the absence of infection or inflammation; *uncertain:* plasma ferritin concentration ≥12 µg/L in the presence of infection or inflammation |
| Plasma soluble transferrin receptor concentration | Continuous | mg/L |
| Plasma C-reactive protein concentration | Continuous | mg/L |
| Plasma *α*_1_-acid glycoprotein concentration | Continuous | mg/L |
| Inflammation | Binary | Plasma concentrations of C -reactive protein (CRP) > 5mg/L and/or α_1_-acid glycoprotein (AGP) > 1g/L |
| Whole blood ZPP concentration | Continuous | μmol/mol haem |
| Erythrocyte ZPP concentration | Continuous | μmol/mol haem |
| *Plasmodium* parasite density (asexual and sexual forms) | Continuous | µL^-1^ |
| *Plasmodium* infection, by rapid dipstick tests | Nominal | No infection; *P. falciparum* (by HRP2 or *P. falciparum*-specific pLDH), other human *Plasmodium* spp. (by pLDH), mixed infection |
| Urinary hepcidin concentration * | Continuous | nmol/mmol creatinine |
| Plasma folate concentration * | Continuous | nmol/L |
| Plasma vitamin B_12_ concentration | Continuous | pmol/L |

* Funds permitting

1. **General issues in the analysis of intervention effects**

Effects are measured by comparing outcomes measured after a particular intervention with those measured if an alternative intervention has been given (counterfactual argument), thus focusing on comparison of end points (instead of before-after measurements within groups). We will estimate effects when possible; P-values, where reported, will be 2-sided. We will avoid hypothesis testing and interpretation of results as ‘significant’ or p<0.05 for reasons reported elsewhere [14,15].

We will describe outcome variables by intervention groups as proportions, means (SD), geometric means (geometric SD), and median (25^th^- and 75^th^ percentiles) as appropriate, with corresponding group sizes. For continuous outcomes, these estimates will be obtained by ANOVA.

Intervention effects will be assessed as absolute differences (proportions and means) or relative differences in geometric means (variables with lognormal distributions) between groups, with accounting for the stratified block design. To facilitate interpretation, odds ratios resulting from these analyses will be converted to differences in proportions. To allow extrapolation of results to other settings, we will also consider reporting relative effects for binary outcomes (i.e. proportion ratios). Outcomes that are not normally distributed, even after log-transformation, will be compared using non-parametric tests (e.g. Mann-Whitney U test, or Wilcoxon rank sum statistics)

1. **Analysis of the primary outcome (objective 1a and 2)**

*Primary analysis:* We will estimate the difference in haemoglobin concentrations at the end of the 30-day fortification period between groups of children allocated to different iron formulations. Non-inferiority will be rejected if the difference between groups is less than the non-inferiority margin.

*Secondary analysis* of the primary outcome will be as follows:

1. *Adjustment* *for selected baseline variables:* Biased effect estimates would occur if there are group imbalances in baseline factors that are prognostic for outcome. For baseline factors that are known to be strongly, or at least moderately, associated with the primary outcome, or for which there is a strong biological rationale for such an association, i.e. iron status, plasma soluble transferrin receptor concentration, and age, we will evaluate the role of such bias using stratified analysis and directly by multiple linear regression models. We also expect haemoglobin concentration at baseline to be prognostic for outcome but, because this will already be accounted for by adjusting for study design. In stratified analysis, we will estimate intervention effects in subgroups formed by these baseline factors (for iron status: see definition in Table 1; plasma soluble transferrin receptor concentration dichotomised with the median as cut-off value; and age in classes of children aged 12-23 months and 24-30 months) to allow an assessment of the validity of model assumptions. In the regression models, we will compare effect estimates with and without adjustment by baseline factors (plasma concentrations of ferritin and soluble transferrin receptor and age; as continuous variables). In the interpretation of data, we will give priority to the unadjusted effect, unless the adjusted effect is markedly different (>15%), in which case the adjusted effect will be considered the primary analysis.

*Subgroup analysis:* Because iron absorption is known to depend on iron status, we will consider proxy markers for iron status (haemoglobin concentration, plasma concentrations of ferritin and soluble transferrin) at baseline as potential modifiers for intervention effects.

Stratified analysis will be used to measure effect sizes within subgroups. Evidence for group differences in intervention effects will be formally investigated in a multiple regression model with main effects (for baseline factors and the intervention) and multiplicative interaction terms.

To define subgroups, baseline factors will be categorized (haemoglobin concentration class <100 g/L and ≥100 g/L; iron status [see classification above] and plasma soluble transferrin receptor concentration [dichotomised, with the median as threshold]). For iron status, we will restrict the analysis to a comparison of iron-deficient and iron-replete subgroups.

Categorisation of baseline factors has the advantage that results can be conveniently presented in a forest plot. It has the disadvantage, however, that the precision of the interaction depends on the number and position of the cut-off values used to categorise baseline factors [16]. We will also explore interactions with baseline factors as continuous covariates, using fractional polynomials [16]. Such a strategy is more powerful, especially at towards extreme ends of the covariate distribution where limited numbers of observations generally preclude detection of interaction, and it may reveal more about the nature of possible interactions. We will inspect scattergrams and conduct sensitivity analysis as needed to examine the influence of possible outliers on results.

Results of subgroup analyses will be interpreted cautiously for reasons reported elsewhere [13].

1. *Intention-to-treat analysis:* For binary outcomes, pooled estimates from multiple iterations may result in non-integer values. This precludes computation of confidence intervals for differences in proportions, and may be counterintuitive to readers not well versed in multiple imputation techniques. To handle this problem, we will calculate differences in means under the assumption of binary outcome variables having a Bernoulli distribution. Pooled chi-squared statistics for cross-tabulated data and associated p-values will be calculated as described by Van Buuren (2012), thus the p-values obtained are only crude estimates of the true values [17].
2. *Paired comparisons of iron groups with placebo (objective 2):* This analysis will be done as for the comparison between iron groups (see above). Superiority will be established if no effect is excluded from the 95% CI.
3. **Analysis of secondary outcomes (objectives 1b and 2)**

To assess intervention effects, we will conduct all three possible paired comparisons between the intervention groups. We will use plasma ferritin concentration as an outcome indicator of iron status, and soluble transferrin receptor as an outcome indicator of the iron demand by the erythrocytes (both measured at the end of the 30-day intervention period). We will conduct analysis with and without adjustment for baseline factors, as well as intention-to-treat analysis (see methods above).

Plasma ferritin concentration has the limitation that it can be enhanced by inflammation independently of iron status. Because our interest in plasma ferritin concentration is limited to its value as a marker of iron status, we will adjust all analysis for inflammation markers (plasma concentrations of C -reactive protein and α_1_-acid glycoprotein; both as continuous variables) measured at the end of the 30-day intervention period. Thus we will effectively measure effects on plasma ferritin concentration assuming no inflammation.

Similarly, plasma soluble transferrin receptor concentration can be elevated by an increased erythropoiesis under influence of malaria-induced haemolysis. Because our interest in plasma soluble transferrin receptor concentration is limited to its value as a marker of tissue iron demand, we will adjust all analysis for inflammation markers (plasma concentrations of C -reactive protein and α_1_-acid glycoprotein; both as continuous variables) measured at the end of the 30-day intervention period.

Stratified analysis will be used to measure effect sizes within subgroups. To assess effect modification directly, we will compare multiple logistic regression models with and without product terms, with categorical baseline factors entered as dummy-coded variables.

1. **Multiplicity**

Multiple comparisons to evaluate non-inferiority (section 6) or to measure effects on multiple secondary outcomes may raise concerns about multiplicity (i.e. occurrence of false-positive results). We consider statistical solutions (e.g. Bonferroni correction) to be inappropriate in our trial because a) the concept of multiplicity is rooted in hypothesis testing, which is not our framework for making inferences; b) we will not formally adjust for multiplicity because any absence or present effect differences will be interpreted by the confidence interval in the context of the set thresholds as defined in section 6 [14,15,12]; c) for an intervention that leads to multiple changes in related outcomes, results from multiple comparisons are mutually reinforcing, not mutually debasing [18] .

In case of substantial discordance in results from analyses to evaluate non-inferiority, we will consider the results to be indeterminate.

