### Additional file 1: Statistical analysis plan

[name], [name]

Version 19^th^ May 2015

1. **Preamble**

This plan was developed to analyse data from the SEICK (Safe and Effective Iron for Children in Kenya) trial. The study received ethical clearance in Kenya (Kenyatta University National Hospital/University of Nairobi, #KNH-ERC/A/402)) and in England (London School of Hygiene and Tropical Medicine, #6503)), and was registered at ClinicalTrials.gov (NCT02073149). The principal features of the planned analysis were established as part of the trial proposal. The current plan provides an update, was finalised after data collection but before breaking the randomization code, and should take precedence over the trial proposal.

1. **Trial objectives**

The study was primarily conceived to assess non-inferiority of daily home fortification with 3mg iron as NaFeEDTA compared with 12.5 mg iron as encapsulated ferrous fumarate, with haemoglobin concentration at the end of the 30-day intervention period as the primary outcome.

The study proposal states the following objectives:

1. In children aged 12-36 months, to compare daily home fortification for 30 days with two iron formulations (3mg iron as NaFeEDTA versus 12.5 mg iron as encapsulated ferrous fumarate) regarding:
2. Haemoglobin concentration at the end of the 30-day fortification period ***(primary objective)***;
3. Iron status at the end of the fortification period;
4. Serum NTBI concentrations at 3 hours after ingesting the first fortificant dose;
5. Faecal calprotectin concentration at the end of the fortification period;
6. *P. falciparum* infection at the end of the fortification period as indicated by whole blood density of asexual parasites or the presence of antigenemia;
7. Adherence to intervention.
8. To compare daily home fortification for 30 days with iron (3mg iron as NaFeEDTA or 12.5 mg iron as encapsulated ferrous fumarate) versus placebo regarding:
   1. The indicators listed under objective 1a-f;
   2. Time to development of anaemia after cessation of iron fortification.
9. To evaluate the accuracy of self-reported adherence with home fortification, using medication events monitoring system as a gold standard.
10. To assess associations between major intestinal parasites and haemoglobin concentration at baseline.
11. To compare intervention effects of iron on intestinal biota.

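### Outcomes that stay non-normal fall back on unstratified rank tests with no effect estimate or interval, against the same section's own rules

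*SAP*

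**What the plan says.** All the rules at issue stand in the SAP section on general issues in the analysis of intervention effects.

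- **Estimation first.** "We will estimate effects when possible; P-values, where reported, will be 2-sided". The next sentence adds: "We will avoid hypothesis testing and interpretation of results as" significant or not.
- **Design.** Effects are absolute differences in proportions and means, or relative differences in geometric means, "with accounting for the stratified block design".
- **Fallback.** "Outcomes that are not normally distributed, even after log-transformation", "will be compared using non-parametric tests (e.g. Mann-Whitney U test, or Wilcoxon rank sum statistics").
- **Description.** "We will describe outcome variables by intervention groups as proportions, means (SD), geometric means (geometric SD), and median" with quartiles. These are summaries per arm.

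Elsewhere, the section on study type and design gives the two randomisation strata (baseline haemoglobin below 100 g/L, and 100 g/L or above). It says that adjusting for them should improve efficiency and precision. Objective 1e is *P. falciparum* infection, indicated by "whole blood density of asexual parasites or the presence of antigenemia". It is not among the objectives set aside for lack of resources (1c, 1d, 4 and 5). ITT analysis uses multiple imputation. The only pooling detail given is for binary and cross-tabulated outcomes.

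**The concern.** The fallback sentence drops what the rest of the section asks for. A Mann-Whitney or Wilcoxon rank-sum test compares two samples as a whole. It has no stratum term and no covariates, and it returns a P-value. An outcome sent there would be reported by a significance test alone, in a plan that rejects significance testing as its basis for inference.

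Two other parts of the SAP depend on having an interval or a model:

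- The multiplicity section declines any adjustment on the ground that results will be read from confidence intervals. An outcome with only a rank-test P-value has none.
- The secondary-outcomes section promises analyses with and without baseline adjustment, and adjusts ferritin and soluble transferrin receptor for C-reactive protein and α1-acid glycoprotein. If either marker stayed non-normal after log-transformation, the named tests could not carry that adjustment.

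The trigger is realistic. Uninfected children have a parasite density of zero, and no log-transformation turns a spike at zero into a normal distribution. The secondary-outcomes section names methods only for ferritin and transferrin receptor, so the general rule is the only one that density could fall under as a quantity.

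**Working it through.** **Inputs from the SAP.** Target of 108 per group, two haemoglobin strata, 20 iterations of multiple imputation (taken here as 20 imputations). The SAP gives no standard deviation or power, so 108 cannot be reproduced; it serves only as the number per arm.

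**Inputs assumed.** Stratum split, infection prevalence, effect size, outcome distribution and missingness are not in the SAP.

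**1. Power and type I error.** The tie-corrected rank-sum test was compared with its stratified form (van Elteren), two-sided 5%, 4000 simulated trials per scenario. The Monte Carlo standard error is at most √(0.5 × 0.5 / 4000) = 0.8 points.

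*Density-like outcome, set A:* 40% of children in the low stratum, log-normal density if infected, odds ratio for infection 0.5.

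| Prevalence, low vs high stratum | Power, unstratified | Power, van Elteren | Difference (points) |
|---|---|---|---|
| 60% vs 15% | 41.8% | 47.7% | 5.9 |
| 50% vs 20% | 51.0% | 53.1% | 2.1 |
| 40% vs 25% | 56.2% | 56.5% | 0.3 |

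Type I error was 2.5% vs 4.9% in the first row and 3.9% vs 5.2% in the second. A separate run of set A gave power of 41.4% vs 46.9%, 51.7% vs 54.1% and 54.3% vs 54.9%.

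*Density-like outcome, set B:* equal strata, prevalence 30% in one stratum and lower in the other, log odds ratio for arm 0.8.

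| Stratum log odds ratio | Power, unstratified | Power, van Elteren | Difference (points) |
|---|---|---|---|
| 0 | 77.9% | 78.2% | 0.3 |
| 0.5 | 75.3% | 75.5% | 0.2 |
| 1 | 69.5% | 70.6% | 1.1 |
| 1.5 | 62.9% | 65.0% | 2.1 |

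The two sets agree. The 60% vs 15% row is a stratum log odds ratio of ln(0.60/0.40) − ln(0.15/0.85) = 0.41 + 1.73 = 2.14, beyond the range of set B.

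*Continuous outcome:* t distribution with 3 degrees of freedom, equal strata, arm shift 0.55.

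| Stratum difference | Type I, unstratified vs van Elteren | Power, unstratified vs van Elteren |
|---|---|---|
| 0 | 5.3% vs 5.4% | 88% vs 88% |
| 0.5 | 4.7% vs 5.1% | 87% vs 88% |
| 1 | 3.1% vs 4.7% | 83% vs 88% |
| 1.5 | 1.9% vs 4.6% | 77% vs 89% |
| 2 | 1.5% vs 4.8% | 67% vs 88% |

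The loss is about 5, 12 and 21 points at differences of 1, 1.5 and 2, and nil when the stratum is not prognostic. The unstratified test is conservative because its variance includes the spread between strata, which balanced randomisation has already removed from the arm comparison.

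**2. Can a rank-based effect be pooled?** The Mann-Whitney probability P(X > Y) + ½P(X = Y) was estimated in each of 20 imputed sets with 10% missing. It was pooled by Rubin's rules, with total variance = mean within-imputation variance + (1 + 1/20) × between-imputation variance. With prevalences of 45% and 30%, the true value is 0.45 × 0.70 + ½ × 0.45 × 0.30 + ½ × 0.55 × 0.70 = 0.575. The pooled 95% CI covered it in 95.0% of 1500 runs, so pooling is feasible.

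**3. Would a Hodges-Lehmann shift supply the estimate?** Take control prevalence 60% and odds ratio 0.5. Treated odds are 1.5 × 0.5 = 0.75, so treated prevalence is 0.75/1.75 = 42.9%. With the same density distribution among the infected:

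- P(control > treated) = 0.6 × 0.571 + ½ × 0.6 × 0.429 = 0.47
- P(treated > control) = 0.429 × 0.4 + ½ × 0.6 × 0.429 = 0.30

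Both are below one half, so the median pairwise difference is exactly 0 although the odds of infection are halved. The shift cannot describe an outcome with many zeros.

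**The case against.** The strongest defence is that the wording leaves room. Effects are to be estimated only where possible, the two tests are given as examples, medians with quartiles are reported by arm, and the fallback sentence follows the promise to account for the design in the same paragraph. A careful analyst could choose a stratified rank method and still comply. That is fair, but the plan does not fix such a choice. Both named examples are unstratified, and a median per arm is not a between-arm effect.

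A reader might infer more than the document supports:

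- *That rank-based results cannot be pooled over imputations.* They can, as shown. The SAP merely gives no rule for it.
- *That the malaria objective would be left with only a P-value.* Infection can be analysed as a proportion, for which the same section plans differences that account for the design. Nor does the SAP assign density to the rank test; that follows only by applying its general rule.
- *That covariate-adjusted and ITT versions are explicitly planned for density.* The sentence promising them stands in a section that names only ferritin and transferrin receptor. It reaches density only if that section's reference to objective 2 is read broadly.
- *That the trial loses much power.* For a density-like outcome it does not, and the error is conservative: false positives are not inflated.

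**Conclusion.** The point holds as a conflict within one section. The stated fallback gives no effect estimate or interval, ignores the randomisation strata and takes no covariates, while the section promises estimation, avoidance of testing and allowance for the design. This conclusion needs no simulation.

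The cost in power is a secondary argument and rests on assumed inputs: about 0 to 6 points for a density-like outcome, where 6 needs a 60% vs 15% prevalence split by stratum, and about 5 to 21 points for a continuous outcome with stratum differences of 1 to 2. If the stratum does not predict the outcome, nothing is lost.

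The reach is limited to outcomes other than the primary one. Haemoglobin is planned as a difference in concentrations, so the non-inferiority decision is untouched.

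**What to change.** Replace the fallback sentence with:

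> Outcomes that remain non-normal after log-transformation will be analysed with a proportional-odds (cumulative logit) model with arm and baseline haemoglobin class, zeros forming the lowest category; the common odds ratio with 95% CI will be reported and its log pooled by Rubin's rules in the ITT analysis.

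The model accepts further covariates wherever an adjusted analysis is planned. An acceptable alternative is a stratified Mann-Whitney probability with its CI, with van Elteren for any P-value. A Hodges-Lehmann shift should not be used for outcomes with many zeros. The SAP should also say whether parasite density is analysed as a quantity under this rule, as infection yes or no, or both.

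The cost is one sentence and a little programming in R, which the software section already lists. The downside is that proportional odds must be checked. In the example above, with an effect on infection alone, the odds ratio is 0.5 at the zero threshold and tends to 0.429/0.6 = 0.71 at very high densities, so the common odds ratio would be an average. The SAP states that it was finalised before the code was broken; fixing the method at that stage avoids a choice made with the results in view.

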The target sample size was 108 participants per group, which was determined using procedures and terminology for sample size calculations in non-inferiority trials as recommended by US Food and Drug Administration [3,4]

1. Based on a meta-analysis [5], we estimated the effect of 12.5 mg ferrous fumarate on haemoglobin concentration relative to placebo. The lower limit of the 95% CI thus obtained (9.3 g/L) was used as M_1_, the minimum anticipated effect of 12.5 mg ferrous fumarate in our trial (**Figure 2;** left panel).
2. Next, we set M_2_ as the margin specified to preserve 50% of the anticipated minimum effect of 12.5 mg ferrous fumarate anticipated reduction in the 3mg NafeEDTA test treatment. This margin (haemoglobin concentration of 4.7 g/L) can be interpreted as the largest loss of effect compared to 12.5 mg ferrous fumarate (inferiority) that would be acceptable, and also is below an effect for 5g/L haemoglobin concentration that we consider to be of minimum importance for public health.
3. We set the sample size so that the lower limit of the 95% CI around the difference in haemoglobin concentration between the two iron formulations (i.e. 12.5 mg ferrous fumarate and 3.0 mg iron as NaFeEDTA) would lie above M2 (Figure 1; right panel).

Peer reviewers or editors of scientific journals may demand that we report sample size calculations and statistical power. Although such calculations are critically important in planning a study, we consider statistical power to be an exclusively pre-trial concept, which is irrelevant and conceptually wrong in the interpretation of study results, based on assumptions that are not usually met during trial implementation, and prone to be misinterpreted by most readers [6,7]. Thus we intend to refrain from reporting sample size calculations, but we will report the method used to determine the non-inferiority margin.

[figure not shown]

Figure S2: Theoretical framework for sample size determination

1. **Software**

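### The sentence that judges non-inferiority compares the difference itself, not a confidence limit, with a margin written without a sign or an order of subtraction

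*SAP*

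**What the plan says.** The SAP section on analysis of the primary outcome opens with the estimate: "We will estimate the difference in haemoglobin concentrations at the end of the 30-day fortification period between groups of children allocated to different iron formulations". The criterion follows at once: "Non-inferiority will be rejected if the difference between groups is less than the non-inferiority margin". Neither sentence says which arm is subtracted from which, and neither mentions an interval.

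The margin comes from the section on sample size calculations. Item 2 sets it as "the margin specified to preserve 50% of the anticipated minimum effect of 12.5 mg ferrous fumarate" and explains: "This margin (haemoglobin concentration of 4.7 g/L) can be interpreted as the largest loss of effect compared to 12.5 mg ferrous fumarate (inferiority". It is thus a positive quantity that measures loss. Item 3 of that section sizes the trial so that "the lower limit of the 95% CI around the difference in haemoglobin concentration between the two iron formulations" "would lie above M2 (Figure 1; right panel". The two formulations are listed there with ferrous fumarate first.

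Three other places bear on the decision:
- The section on intention-to-treat versus per protocol analysis accepts non-inferiority only if efficacy over placebo, assay sensitivity and non-inferiority are all shown. It compares the results of both analysis sets.
- The item on paired comparisons with placebo judges superiority by the 95% CI.
- The multiplicity section says that effects will be read from the confidence interval against thresholds set in section 6.

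**The concern.** A non-inferiority claim needs three things fixed before unblinding: the direction of the difference, the signed margin, and the confidence limit compared with it. The sentence for the primary comparison fixes none of them. It also does not match the sample-size section, which works with a confidence limit.

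With a margin of +4.7, a difference of zero is below the margin, so two equally good products fail. If the reader turns the margin into −4.7 but applies the sentence to the difference itself, sampling error is ignored and a product exactly at the unacceptable loss passes half the time. The SAP states that it takes precedence over the trial proposal, so the proposal cannot be relied on to override this wording. Different readings can give different verdicts on the same data, and the choice between them would be open after the code is broken.

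**Working it through.** **Inputs from the SAP.** M1 = 9.3 g/L, 50% of the effect preserved, margin 4.7 g/L, 108 participants per group (all from the section on sample size calculations).

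**The plan's own figures.** The margin reproduces: 0.5 × 9.3 = 4.65, rounded to 4.7. The group size cannot be reproduced, because the SAP gives neither SD nor power; that is not raised here. With a one-sided 2.5% level and no true difference, 108 per group implies SD = 4.7 / [(1.96 + z_power) × √(2/108)]. This is 12.3 g/L at 80% power and 10.7 g/L at 90%.

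**Assumption.** SD of 10 to 14 g/L, which covers those implied values. SE = SD × √(2/108) = SD × 0.136, so SE is 1.36 to 1.91 g/L and the 95% half-width is 2.67 to 3.73 g/L.

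**Chance of meeting the non-inferiority component** (Φ is the normal distribution function, D the true NaFeEDTA minus ferrous fumarate difference):

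| Reading | Formula | D = 0 | D = −4.7 | D = −6 |
|---|---|---|---|---|
| Ferrous fumarate minus NaFeEDTA, +4.7, point estimate | Φ((−D − 4.7)/SE) | 0.03–0.7% | 50% | 75–83% |
| NaFeEDTA minus ferrous fumarate, +4.7, point estimate | Φ((D − 4.7)/SE) | 0.03–0.7% | <0.01% | <0.01% |
| NaFeEDTA minus ferrous fumarate, −4.7, point estimate | Φ((D + 4.7)/SE) | 99.3–99.97% | 50% | 17–25% |
| NaFeEDTA minus ferrous fumarate, −4.7, lower 95% CI limit | Φ((D + 4.7)/SE − 1.96) | 69–93% | 2.5% | 0.2–0.4% |

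Worked entries at SD 10:
- Literal reading, D = 0: Φ(−4.7/1.36) = Φ(−3.45) = 0.03%.
- Point estimate against −4.7, D = −6: Φ(−1.3/1.36) = Φ(−0.96) = 17%.
- CI limit, D = −6: Φ(−0.96 − 1.96) = 0.2%.

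The first row is a reversed rule: equal products fail and larger losses pass. The second asks for a gain of 4.7 g/L. The third has the right direction but no allowance for sampling error.

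**Results on which the last two rows disagree.** With the CI limit, the observed difference must exceed −4.7 + 2.67 = −2.0 g/L at SD 10, or −4.7 + 3.73 = −1.0 g/L at SD 14. Any observed difference between −4.7 and that value passes on the point estimate and fails on the interval.

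**With the placebo conditions added.** A simulation of three arms of 108, assuming a ferrous fumarate effect of 9.3 g/L, required both iron arms to beat placebo by the 95% CI. Under the point-estimate rule with −4.7, acceptance was about 41–49% at a true loss of 4.7 g/L and 15–17% at 6 g/L. Under the CI rule it was about 2.4–2.5% and 0.2–0.4%. Under the literal reading, equal products still passed less than 1% of the time. The comparison of intention-to-treat and per protocol results was not simulated.

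**The case against.** The best defence is that the intended rule can be recovered. Item 2 of the sample-size section defines the margin as a loss against ferrous fumarate, so the reference product and the harmful direction are settled; only the algebraic sign is unwritten. A margin expressed as a positive loss is not an error in itself. Item 3 uses the lower 95% limit, and the multiplicity section says that results are read from the confidence interval. The figure cited in item 3 is not shown in the text at hand and may display the axis and the place of M2. The placebo comparisons and the two analysis sets are further safeguards.

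Much of this stands, and it rules out some stronger readings:
- *That this is the sole rule for the primary objective.* It is the sole criterion for one component; overall acceptance has further conditions.
- *That the direction is never fixed.* The definition of the margin as a loss fixes it in words, and the missing figure may do more.
- *That the error rates in the table are those of the final conclusion.* They apply to the non-inferiority component only. The placebo conditions would stop most very large losses: if NaFeEDTA were no better than placebo, its own superiority test would pass only 2.5% of the time.
- *That the sponsor meant to test on the point estimate, or that a wrong verdict was reached.* The document points to an interval rule and contains no results.

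The defence does not repair the sentence. Item 3 concerns sizing, and its text also leaves the margin unsigned: a lower limit above +4.7 would show that one formulation beats the other by more than 4.7 g/L. By heading order, section 6 is the one on intention-to-treat versus per protocol analysis, which holds no haemoglobin threshold and no CI criterion. Near the margin, the placebo conditions lower false acceptance only modestly.

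**Conclusion.** The point holds as a defect in the wording of the non-inferiority criterion, and it matters because that criterion decides the primary comparison. Followed literally, it rejects non-inferiority for identical products in 99.3–99.97% of trials. That figure shows that the wording cannot be applied as it stands; it is not a forecast of what the analysts would do. The more realistic risk is a reader who corrects the sign and keeps the point estimate, which raises false acceptance at the margin twentyfold (50% / 2.5% = 20).

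The 50% and 2.5% for the component hold for any SD under the normal approximation. The other rates rest on the assumed SD of 10–14 g/L and on 108 analysed per arm, and the overall acceptance rates also on a 9.3 g/L ferrous fumarate effect.

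**What to change.** In the section on analysis of the primary outcome, replace the criterion with:

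> Difference = mean haemoglobin (3 mg NaFeEDTA) minus mean haemoglobin (12.5 mg ferrous fumarate). The non-inferiority component is shown if the lower limit of the two-sided 95% CI lies above −4.7 g/L; otherwise it is not shown.

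Keep the existing conditions for overall acceptance (efficacy, assay sensitivity, and the comparison of both analysis sets). In item 3 of the sample-size section, use the same order of subtraction and write the margin as −4.7 g/L. In the multiplicity section, point the reference to thresholds at the section that now holds the rule.

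The cost is two sentences and a corrected cross-reference. No data, model, margin or sample size changes.
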